**Methods:**

Healthy volunteers between the ages of 6 and 35 years will be enrolled across two sites. Participants will complete a conditioning task in a novel virtual reality environment, allowing for control over pre-exposure and the examination of behaviour. A dental startle (a brief, pressurized puff of air to a tooth) will serve as the unconditioned stimulus. Using a within-subjects experimental design, participants will experience a pre-exposed to-be conditioned stimulus, a non-pre-exposed to-be conditioned stimulus, and a neutral control stimulus. Two hypothesized mechanisms, changes in prediction errors and attention, are expected to mediate the association between stimulus condition and fear acquisition, recall, and retention. To ascertain the involvement of pain sensitivity, this construct will be measured through self-report and the cold pressor task.

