## Methods and analyses

### Participants and setting

Participant enrollment will occur at two university sites—one in northwest Ohio and one in south Texas. Based on a power analysis, we aim to recruit 100 participants from the general community, ranging in age from 6 to 35 years old. Full eligibility requirements are presented in Table 1. Participants will complete two in-person study visits and receive a $50 gift card at each visit completed.

**Table 1 Tab1:** Participant eligibility criteria

Inclusion criteria	Exclusion criteria
Be between the ages of 6 and 35 years old	Currently have glasses or use contact lenses with a vision correction of ≥ ± 6
At least 2 of their maxillary anterior 6 teeth present	Are colorblind
All of their maxillary anterior 6 teeth are stable	Current injury (including fractures, open cuts, or sores) on their dominant hand
All of their maxillary anterior 6 teeth are free of cavities	Fixed dental or orthodontic appliance that would interfer with creating a mouthpiece
All of their maxillary anterior 6 teeth are free of hypersensitivity to pain or pressure	Diagnosis by a dental/oral health professional of Temporomandibular Disorder (TMD) along with a history of exacerbation of symptoms resulting from routine dental procedures
Able to read, write, and converse in English (English or Spanish at Texas site)	Currently on any anti-anxiety or anti-depressant medications
Willing and able to provide a signed and dated informed consent/assent form to participate	Currently have an inner ear infection
Willing and available to comply with all study procedures and available for the duration of the study	Living in the same household or an immediate family member of an enrolled participant
	Currently have a cardiovascular disorder or a pacemaker
	Currently have a seizure disorder or epilepsy
	History of frostbite or sensitivity to extreme cold
	Bleeding disorder or take blood thinners
	Vasospastic disorder such as Raynaud's syndrome or Raynaud's disease
	Gastrointestinal or vestibular disorders that may elevate susceptibility to nausea and dizziness such as Meniere's disease, hyperemesis gravidarum or severe migraines
	Negative outcome with VR simulation
	Medical or psychological condition that requires them to avoid mild stress
	Any medical condition that elevates risk of falls, dizziness, nausea, or causes a vasovagal reaction
	Any other general or oral health concerns

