Inasmuch as learning effects cannot be seen until the conditioning phase, this hypothesis is tested only during the conditioning, recall, and retention phases. To test hypothesis 1b, the conditioning phase and recall and retention phase analyses described above will be conducted with indicators of fear learning (fear ratings, approach behaviour, and skin conductance response) serving as the dependent variables. In cases in which there are multiple measurements (i.e., fear ratings, skin conductance) scores will be averaged within each phase.

Hypothesis 2: Changes in prediction errors and attention will mediate the effects of pre-exposure on fear acquisition, recall, and retention.

To test the second hypothesis, three sets of multilevel mediation models [19, 20] will be estimated to test for mediation of the fear acquisition, recall, and retention effects. Each mediation analysis will include stimulus type (dummy-coded) and the two candidate mediators—prediction errors and attention.

Parameters will be obtained by maximum likelihood estimation with robust standard errors, a procedure that is robust to violations of normality and heteroscedasticity and obtains optimal parameter estimates when response data are incomplete [21, 22], with indirect effects tested by a z test. However, given the z test may be underpowered, we will double-check results by also using Bayesian estimation, which provides for improved inference via 95% credible intervals for indirect effects [23, 24].

Hypothesis 3. Higher pain sensitivity will be associated with greater engagement of the targeted mechanisms and greater LI of conditioned fear acquisition, recall, and retention.

To test the third hypothesis, individual differences in pain sensitivity will be included in the above analyses as a moderating variable.

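### Hypothesis 2 is tested with a z test that the plan itself suspects of low power, the credible interval it calls better inference serves only as a check, and no rule says which decides

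*Protocol article*

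**What the plan says.** The Analyses section of the protocol article, under Hypothesis 2, plans "three sets of multilevel mediation models", one set each for fear acquisition, recall and retention. "Each mediation analysis will include stimulus type (dummy-coded) and the two candidate mediators", namely prediction errors and attention. Estimation is by maximum likelihood with robust standard errors, "with indirect effects tested by a z test". The next sentence reads: "However, given the z test may be underpowered, we will double-check results by also using Bayesian estimation". It goes on to describe that second analysis in favourable terms, as one "which provides for improved inference via 95% credible intervals for indirect effects".

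The sample size is given under Participants and setting: "Based on a power analysis, we aim to recruit 100 participants from the general community". The article reports no effect size, power, alpha or target test for that analysis, and no expected size for either mediation path.

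**The concern.** An indirect effect is a product of two estimated paths. When both paths are modest relative to their standard errors, that product is skewed and a normal-theory z test is conservative. The article recognises the problem but keeps the z test as the named test. It gives the interval, which it describes more favourably, a supporting role.

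The stated reason for the second analysis is low power. The case it exists for is therefore a non-significant z with an interval that excludes zero, and that is the case the text does not resolve. Read literally, Hypothesis 2 is decided on the weaker test. Read by its rationale, the interval should decide. The choice could then be made after both results are known. Hypothesis 2 carries the study's main aim, which is to identify the mechanisms by which pre-exposure slows fear learning.

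**Working it through.** **Inputs from the article.** Sample size 100 (Participants and setting). "Using a within-subjects experimental design" (abstract, Methods). Two mediators and three phases (Analyses), so at least 3 × 2 = 6 indirect effects before counting separate fear indicators or stimulus contrasts. The figure of 100 cannot be reproduced, because the inputs to the power analysis are not given.

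**Assumptions.** Two-sided alpha 0.05; two conditions reduced to within-person differences; one mediator; residual variances of 1; flat priors; no random slopes; no missing data. Path a is the standardised mean change in the mediator. Path b is set through a partial correlation r, with b = r/√(1 − r²).

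**Model and tests.** dM = a + e₁ and dY = c + b·dM + e₂. The z test is z = âb̂ / √(â²·v_b + b̂²·v_a), compared with 1.96. The credible interval is the 2.5th to 97.5th percentile of the posterior of a·b (4,000 draws). There were 3,000 simulated studies per setting.

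**Why z is conservative here.** Take a = 0.25 and r = 0.25, so b = 0.25/√0.9375 = 0.258. With n = 100 each standard error is about 1/√100 = 0.1, and the two paths sit at about 2.5 and 2.58 standard errors. Both exceed 1.96, yet z = (2.5 × 2.58)/√(2.5² + 2.58²) ≈ 6.45/3.59 ≈ 1.80, which does not.

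**Results at n = 100.**

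| a / r | z positive | interval positive | disagree |
|---|---|---|---|
| 0 / 0.30 | 1.5% | 3.8% | 2.3% |
| 0.50 / 0 | 3.4% | 5.2% | 1.8% |
| 0.20 / 0.14 | 4.8% | 12.3% | 7.5% |
| 0.20 / 0.20 | 9.6% | 22.7% | 13.2% |
| 0.25 / 0.25 | 27.5% | 46.3% | 18.8% |
| 0.30 / 0.30 | 54.8% | 71.5% | 16.7% |
| 0.35 / 0.35 | 79.0% | 87.5% | 8.5% |
| 0.40 / 0.40 | 93.2% | 96.3% | 3.0% |
| 0.50 / 0.20 | 43.3% | 50.5% | 7.1% |
| 0.50 / 0.50 | 99.8% | 99.8% | 0.0% |
| 0.80 / 0.30 | 85.5% | 86.3% | 1.2% |

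A significant z with an interval covering zero occurred in at most 0.3% of studies in any setting.

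**Second simulation.** With 4,000 studies per setting and a Monte Carlo interval for a·b standing in for the Bayesian one, power for z against the interval was 26% v 45% at 0.25/0.25, 52% v 71% at 0.30/0.30 and 74% v 86% at 0.35/0.35. Disagreement was 20%, 18% and 12%. The gap between the two runs at 0.35 is of the size expected if the second path is scaled as a slope rather than a partial correlation: r = 0.35 corresponds to a slope of 0.35/√0.8775 = 0.374. Taking both runs together, the power loss for equal paths of 0.20 to 0.35 is about 8 to 19 points.

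**Across six indirect effects**, treated as independent, the chance of at least one conflict is 1 − (1 − p)⁶: 17% at p = 3%, 37% at p = 7.5% and 67% at p = 17%.

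**False positives.** With a null indirect effect, calling mediation if either method is positive gave 0.1% to 5.2% in the first simulation. In a further check the interval alone reached at most about 5.7%.

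**The case against.** The strongest reply is that an order is already stated: the z test is the named test and the Bayesian analysis is a check. That stands in part, since z has nominal priority. It does not settle the matter, because the same passage says z may lack power and presents the interval as the better inference. Keeping that order also means accepting the power loss shown above.

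A second reply is that priors and tie-break rules commonly sit in a statistical analysis plan, which is not shown. That is fair for the priors, and their absence from the article is not a fault. The point here concerns what the article does fix: the weaker of two planned analyses is named as the test.

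A reader might infer three stronger things that the documents and the checks do not support:

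- **That the two methods will often disagree at n = 100.** The article gives no path sizes, so nothing places this trial in the range where disagreement peaks. Even at that peak the methods agree in about 80% of studies per indirect effect.
- **That the z test is far too conservative in general.** At 0.40/0.40 its power is 93.2% against 96.3%.
- **That an open criterion inflates false positives.** Disagreement runs almost entirely one way, so taking the more favourable result amounts to using the interval, whose error rate for a single effect is near or below 5%.

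It is also true that the simulations are not the planned model. Multilevel models with two mediators, repeated trials, random slopes or informative priors could shift the rates in either direction.

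**Conclusion.** The point holds in a limited form. The article makes the z test the named test of mediation while doubting its power, demotes the interval it prefers to a check, and does not say which decides. The cost depends on the paths. It is greatest when both are about 0.2 to 0.35, and smaller when one is small and the other large (7.1% disagreement at 0.50/0.20). It is about 5% or less when a path is null or both are 0.4 or larger. These figures rest on assumed path sizes, difference scores, a single mediator and diffuse priors, and should be read as illustrative. What is at stake is avoidable loss of power and a criterion left open for the central hypothesis, not type I error for a single effect.

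**What to change.** State under Hypothesis 2 that the 95% Bayesian credible interval for each indirect effect, with priors fixed before the data are analysed, is the decision criterion, and that the maximum-likelihood z test is reported as a sensitivity result. Both analyses are already planned, so the change is about one sentence. The added cost is that the priors must be specified in advance, and a short prior-sensitivity check may be needed. If the investigators prefer to keep the z test as the criterion, saying so outright would also close the ambiguity, but with the power loss described above.

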## Discussion

This protocol describes the design of a study to test hypotheses regarding the mechanisms through which pre-exposure interventions result in LI of conditioning to a noxious oral stimulus. Additionally, the ability of a relevant individual difference variable, pain sensitivity, to predict the magnitude of LI via engagement of the hypothesized mechanisms will be tested. Results from this study could be used to design prevention programs for dental phobia and to predict for whom these programs will be most effective.

A practical issue that could affect study quality include the possibility that assessment of the variables of interest through participant ratings could either facilitate or interfere with the learning taking place in the conditioning task and/or the physiological assessment of fear learning. There is some evidence, however, that these effects can be minimized or eliminated through intermittent (i.e., not on every trial) ratings and careful timing of the rating and physiological measurements [25]; therefore, that is the approach utilized here. A second possible issue is the reliable execution of study procedures across the two study sites. Given that the study intervention is automated using an identical VR program at both sites, the concerns here are greatly minimized. Detailed standard operating procedures and training requirements will also be used to maximize fidelity.

## Data Availability

Not applicable.

## Abbreviations

ANOVA: Analysis of variance
CS^−^: Never-conditioned stimulus
CS^+^_NP_: Non-pre-exposed to-be conditioned stimulus
CS^+^_P_: Pre-exposed to-be conditioned stimulus
LI: Latent inhibition
ms: Millisecond
psi: Pounds per square inch
UCS: Unconditioned stimulus
